2. Estimate the effect of the innovative idea of providing breastfeeding support including the use of culturally appropriate educational messages and metaphors in well-child clinics as the “community’ basis of Step 10, in combination with the implementation of BFHI steps 1-9 in maternities on the rate of exclusive breastfeeding at 6 months
3. **Project Design and Implementation Plan**

This will be a randomized controlled trial using cluster randomization. The unit of randomization will be health facilities (cluster) as the experimental or control interventions will be delivered at the level of maternity and well-child clinic of each participating health facility. The study will be conducted in Kinshasa, the capital of the DRC. BFHI is not being implemented to any extent today in DRC. The main attempt to implement BFHI steps in DRC was let by UNICEF in early 2000s as part of a national campaign of breastfeeding promotion, Overall 25 out of more than 6,000 health facilities eligible were certified through this effort including 13 in Kinshasa. The last hospital certified was in 2004 in the Katanga province when the funding stopped. Just two years after the peace deal that ended the deadliest war since World War II, which, in addition to decades of gross mismanagement and rampant corruption, have left the country infrastructures in shambles (32,33), DRC was simply not ready to take over the initial UNICEF efforts. Currently, pregnant women attending antenatal clinic (ANC) as well as nursing mothers attending well-child clinic visits are given some information about the benefits and management of breastfeeding. But there are no quality of care steps being implemented and where it exist, the supporting materials to carry out effective counseling of mothers date from the UNICEF supported campaign 10 years ago.

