Since 2002 and under the leadership of [name], the University of North Carolina at Chapel Hill (UNC) has collaborated with the Congolese Ministry of Health (MoH) and national and local organizations to improve Human Immunodeficiency Virus (HIV) prevention and care through the University Technical Assistance Program (UTAP) with support from various donors. Currently, 44 maternities are supported by our UNC-DRC team serving more than 50,000 pregnant women yearly. These maternities are generally part of a health facility that also hosts a well-child clinic where infants are typically monitored on a monthly basis. As stated above, routine immunization takes place during these monthly visits. To minimize the implementation cost, six of the 44 health facilities with the largest number of deliveries per year will be selected to be part of the study – 3 in urban and 3 in peri-urban areas. Prior to selection, direct observation will be carried out in eligible health facilities to collect information on key characteristics (workload per staff, type of management [government vs private], general infrastructure) that are likely to affect the quality of care. Facilities will be matched for these characteristics prior to randomization. This approach will ensure for example, that health care facilities at the periphery of the city that might have lower patient volumes than facilities in urban areas and serve populations more likely to be socio-economically disadvantaged are included. The selected six facilities will be randomized into 3 groups to receive the following interventions: 1) continuation of current care practices (usual care), 2) implementation of BFHI steps 1-9 in maternities (BFHI steps 1-9), and 3) implementation of BFHI steps 1-9 in maternities and provision of breastfeeding support including culturally appropriate educational messages and metaphors as the ongoing aspect of step 10 in well-child clinic (BFHI steps 1-9 +well-child clinic). The study will be implemented in 2 phases.

Pre-intervention phase

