Data from the questionnaires will be double entered into an Access database, compared for consistency and cleaned as needed. The proportion of infants initiating breastfeeding within 1 hour of birth and who are exclusively breastfed at 14 weeks and 6 months post-partum are the primary outcomes that will be measured and compared between intervention and control groups. To estimate the effect of implementing the *Ten Steps* in maternities on the rate of breastfeeding initiation within 1 hour of birth and that of exclusive breastfeeding at 6 months, the usual care group will provide the counterfactual, and the proportion of infants with each of the primary outcomes in the BFHI steps 1-9 group will be compared to the proportion of infants with the same outcomes in the usual care group. To determine the effect of providing breastfeeding support in well-child clinics in addition to implementing the Steps 1-9 in maternities on the rate of EBF at 6 months, the BFHI steps 1-9 group will serve as control and the proportion of infants with the outcome in the intervention group ( BFHI steps 1-9+well-child clinic) will be compared to that of infants with the outcome in the BFHI steps 1-9 arm.

All analyses will be conducted by intent-to-treat (38), meaning that mother-infant couples will be classified to have received the intervention that their facility was randomized to whether they continued to come to the facility or not after initial discharge from the maternity and the level of uptake of the *Ten Steps* in the facility. Baseline characteristics of mother-infant pairs will be compared between interventions and control groups to check for any imbalance that may persist despite randomization. Pearson chi-square will be used to compare categorical variables and T-test will be used for continuous variables assuming they are normally distributed. Normality will be formally evaluated using Kolmogorov–Smirnov test. For non-normally distributed continuous variables, Wilcoxon Rank-sum test will be used. Generalized Estimation Equation (GEE) and Log Binomial model will be used to estimate the prevalence ratio comparing interventions groups to controls. In GEE, the dependence within cluster is treated as nuisance, and valid inference (or confidence interval) is produced for population average effects as long as the mean structure is correctly specified, even if the dependence structure is misspecified (39).

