The sample size of 150 mother-infant pairs per maternity is based on a series of power calculations using various prevalence estimates of the prevalence of EBF at 6 months in the control group (15% to 35% for usual care) and a minimum expected effect size of RR = 1.5 for the first objective – comparison of BFHI steps 1-9 to usual care (figure 2.a) and a prevalence of EBF at 6 months in the BFHI steps 1-9 group of 45 to 65% and a minimum expected effect size of RR = 1.3 for the second objective – comparison of the provision of support in the well-child clinics in addition to the implementation of BFHI steps 1-9 in maternities vs. BFHI steps 1-9 in maternities alone (figure 2.b). Assuming two-tailed Person chi-square test with α values of .05, the sample size of 900 mother-infant pairs should provide adequate power to detect a modest difference in the proportion of infants exclusively breastfed at 6 months between BFHI alone and usual care arms or between BFHI steps 1-9 + well-child clinics arm and BFHI steps 1-9 alone.

To determine the number of clusters of size n = 150 that will be needed to achieve an 80% power, we used the formula proposed by Hayes and Bennett (40). Assuming a coefficient of variation of 25% (which is generally considered reasonable), and a 20% prevalence of exclusive breastfeeding in the “usual care” group, we varied various expected prevalence of EBV that could be achieve with the implementation of the Ten Steps. Results are presented in the figure 3 below. Once the prevalence of EBF in the intervention group reaches 40%, the number of clusters needed falls below 4.

**Figure 2.** Power estimate curves for: a- detecting a minimum effect size of RR = 1.5 comparing the prevalence of EBF at 6 months in the BFHI steps 1-9 group to that in the usual care group and b- detecting a minimum effect size of 1.3 comparing prevalence of EBF at 6 months in BFHI steps 1-9 + well-child clinic group to that in BFHI steps 1-9 group for a sample of n = 150 per health facility, n = 300 per randomization group, and n = 900 total for various prevalences of exclusive breastfeeding at 6 months.

Figure 3. Number of clusters of size 150 needed to achieve 80% power for a fixed coefficient of variation of 0.25 by the expected proportion of EBF in the intervention group, assuming a 20% prevalence of EBF in the usual care group.

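### The baseline tests treat mothers as independent although facilities are randomised, so their p-values are too small; by how much depends on a between-facility variation the protocol does not give

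*Protocol*

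**What the plan says.** Under Project Design and Implementation Plan, the health facility is the unit of randomisation, and "The selected six facilities will be randomized into 3 groups", that is, two per arm. Under Evaluation, the caption of Figure 2 gives the numbers: "n = 150 per health facility, n = 300 per randomization group, and n = 900 total".

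The analysis paragraph of Evaluation then plans the baseline check: "Baseline characteristics of mother-infant pairs will be compared between interventions and control groups to check for any imbalance that may persist despite randomization". The tests are: "Pearson chi-square will be used to compare categorical variables and T-test will be used for continuous variables". Normality is to be assessed by a Kolmogorov-Smirnov test. "For non-normally distributed continuous variables, Wilcoxon Rank-sum test will be used".

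The same paragraph names GEE with a log-binomial model and discusses dependence within clusters, but only for the prevalence ratio of the outcomes. The sample-size text assumes a between-facility coefficient of variation of 25% in its cluster calculation for EBF. Neither is carried over to the baseline comparison.

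**The concern.** All three tests take their standard error from about 300 independent mothers per arm. What was allocated was two facilities per arm. If mothers at one facility resemble each other more than mothers at another, the difference between arms varies more than the tests assume, and p falls below 0.05 too often when only chance separates the arms. The protocol itself expects such variation: it notes that facilities at the edge of the city may serve poorer populations.

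The check has a real purpose here. Mothers are recruited after facilities have been randomised and staff trained, and masking is not possible, so the baseline table is where differential recruitment would show. A test that often flags ordinary facility differences cannot separate them from a recruitment problem, and its p-values would mislead a reader of that table.

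**Working it through.** **Inputs from the protocol.** Two facilities per arm; m = 150 mothers per facility; between-facility coefficient of variation k = 0.25 and usual-care EBF prevalence 20% (sample-size text).

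**Assumptions.** Two-sided 5% level: the protocol states it for the power calculation and gives none for the baseline tests. The k or ICC of a baseline characteristic: not given, so a range is shown.

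**Step 1. Reproduce the plan's own use of k.** The Hayes-Bennett formula for clusters per arm at 80% power, 20% against 40%, is

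c = 1 + (1.96 + 0.84)² × [p0(1−p0)/m + p1(1−p1)/m + k²(p0² + p1²)] / (p0 − p1)²

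= 1 + 7.849 × [0.00107 + 0.00160 + 0.0625 × 0.20] / 0.04 = 3.98.

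This agrees with the protocol's statement that the number needed falls below 4 at 40%, so k is being read as the protocol uses it.

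**Step 2. Convert k to an ICC and a design effect.**

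ICC = k² p/(1−p) = 0.0625 × 0.20/0.80 = 0.0156

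DE = 1 + (m−1) × ICC = 1 + 149 × 0.0156 = 3.33

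**Step 3. Rejection rate of the unadjusted test with no true arm difference.**

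Rate = 2 × [1 − Φ(1.96/√DE)] = 2 × [1 − Φ(1.074)] = 28.3%

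**Step 4. The same formula over a range, without matching.**

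| Assumption for the characteristic | ICC | DE | Rejection rate |
|---|---|---|---|
| k = 0.10, prevalence 17% | 0.0020 | 1.31 | 9% |
| k = 0.10, prevalence 45% | 0.0082 | 2.22 | 19% |
| k = 0.25, prevalence 10% | 0.0069 | 2.03 | 17% |
| k = 0.25, prevalence 20% | 0.0156 | 3.33 | 28% |
| k = 0.25, prevalence 30% | 0.0268 | 4.99 | 38% |
| ICC set directly | 0.001 | 1.15 | 7% |
| ICC set directly | 0.01 | 2.49 | 21% |
| ICC set directly | 0.05 | 8.45 | 50% |

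**Step 5. Check by simulation** (two facilities of 150 per arm; beta-binomial for chi-square, normal random effects for the other two tests).

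| ICC | Chi-square | t-test | Rank-sum |
|---|---|---|---|
| 0.01 | 21.3% | 22.0% | 21.4% |
| 0.0156 | 28.3% | 28.7% | 27.9% |
| 0.05 | 50.6% | 51.2% | 50.0% |

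All three tests behave alike, so the choice between t-test and rank-sum makes no practical difference to the problem.

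**Step 6. Effect of matching.** If matching removed a fraction f of the between-facility variance from the arm comparison, DE becomes (1 − ICC) + 150 × ICC × (1 − f). With f = 0.5:

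- ICC 0.0156: DE = 0.984 + 1.172 = 2.16, rate 18%.
- ICC 0.05: DE = 0.95 + 3.75 = 4.70, rate 37%.

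The protocol gives no basis for f.

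**The case against.** The best case against the point concerns its size and its consequences, and most of it stands.

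- **The size is not in the protocol.** The coefficient of 0.25 is an assumption about EBF, an outcome. It does not transfer cleanly, because a coefficient of variation depends on how a binary variable is coded. The protocol puts literacy above 91%. With k = 0.25, counting the illiterate 9% gives ICC 0.0625 × 0.09/0.91 = 0.006 and a rate of about 16%; counting the literate 91% gives ICC 0.63 and about 84%, on the same data. A reader might infer from the 28% to 50% figures that a quarter to a half of balanced characteristics will be declared imbalanced. The documents do not support that as a flat statement.
- **Matching.** Facilities are to be matched on workload, management and infrastructure before randomisation. This could lower the rates by an unknown amount.
- **Consequences.** A reader might infer that flagged variables will enter the outcome model. The protocol sets no threshold for the baseline tests and no adjustment rule, and the outcome estimate comes from GEE. Data-driven adjustment is a risk, not a stated plan.
- **Kolmogorov-Smirnov.** A reader might infer that this step has the same fault. It is a normality check, not an arm comparison, and nothing above tests it. It becomes redundant only because it chooses between two tests that should go.
- **A statistical analysis plan may refine this.** It may exist and is not shown. But the protocol does not leave the matter open: it names the tests, and they do not fit the design.

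None of this makes the named tests valid when facilities differ.

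**Conclusion.** The point holds as a mismatch between stated tests and design: individual-level tests are specified for a comparison in which two facilities per arm were allocated, and their p-values are too small whenever a characteristic varies between facilities. The direction is certain under that condition; the size is conditional. At a nominal 5% level and without matching, it is about 28% if the EBF coefficient of 0.25 applied at 20% prevalence. With a coefficient of 0.10 it is 9% to 19%. Over an ICC of 0.01 to 0.05 it is 21% to 50%, and it approaches 5% as the ICC approaches zero. Effective matching lowers each figure.

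The reach is limited to the baseline table and how it is read. The documents do not support a claim that the primary estimate is biased by these tests or that they drive covariate adjustment. The correction is still worth making, because the stated analysis is wrong for the design and changing it costs almost nothing.

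**What to change.** In the analysis paragraph of Evaluation:

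1. Delete the chi-square, t and rank-sum tests of baseline characteristics, and with them the Kolmogorov-Smirnov step.
2. Tabulate baseline characteristics by arm and by facility, and judge imbalance by its size.
3. State that adjustment covariates will not be selected from baseline p-values.

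A facility-level test would be valid in principle but is no useful substitute. With two facilities against two there are only 6 possible splits, so the smallest two-sided permutation p-value is 2/6 = 0.33. With six facilities, the facility columns show the reader directly whether an arm difference comes from one site or both.

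The cost is a change of protocol wording, and the baseline table loses its p-values. Sample size, data collection and the outcome model are untouched.

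### The protocol declares GEE inference valid given only a correct mean model, but with two facilities per arm the usual robust analysis would not hold its 5% level

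*Protocol*

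**What the plan says.** The Project Design and Implementation Plan makes the health facility the unit of randomization and states: "The selected six facilities will be randomized into 3 groups to receive the following interventions". The legend to Figure 2 gives the sizes as "n = 150 per health facility, n = 300 per randomization group, and n = 900 total". Dividing 300 by 150 gives two facilities per arm, hence four per pairwise comparison. Before that, "Facilities will be matched for these characteristics prior to randomization".

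For the primary outcomes, the Evaluation section says: "Generalized Estimation Equation (GEE) and Log Binomial model will be used to estimate the prevalence ratio comparing interventions groups to controls". It then says that "valid inference (or confidence interval) is produced for population average effects as long as the mean structure is correctly specified", adds that this holds even under a wrong dependence structure, and cites a note on robust variance estimation. The number of clusters is not mentioned as a condition, and neither a small-sample correction, a reference distribution nor a matching term is named. The level comes from the sample size paragraph: "Assuming two-tailed Person chi-square test with α values of .05".

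**The concern.** Robustness to a wrong dependence structure is a large-sample property in the number of clusters. Adding mothers within facilities does not supply it. With two facilities per arm, the sandwich estimate rests on one between-facility difference in each arm, is biased downwards, and is too unstable for a normal reference distribution.

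The sentence bears on the confidence intervals for both primary objectives. If the analysis is run in the form the sentence describes, ordinary differences between facilities will often be reported as effects of BFHI steps 1-9 or of the well-child clinic support. The Sustainability and Potential for Scaling-Up section ties a positive result to wide scale-up.

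**Working it through.** **Inputs from the protocol.** Two facilities per arm; 150 mothers per facility, 135 after 10% loss; two-sided level 0.05; coefficient of variation (CV) between facilities 0.25; usual-care prevalence of exclusive breastfeeding 20% (17% in the 88% power statement).

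**Assumed, because the protocol names neither.** Uncorrected sandwich variance and normal quantiles.

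**The plan's own cluster count.** The cited formula is c = 1 + (1.96 + 0.84)² × [p0(1−p0)/n + p1(1−p1)/n + CV²(p0² + p1²)] / (p0 − p1)². For 20% vs 40%, n = 150 and CV 0.25:

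c = 1 + 7.85 × (0.00107 + 0.00160 + 0.01250) / 0.04 = 3.98.

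This reproduces the statement that fewer than 4 clusters are needed. The formula counts clusters per arm, and the trial has two.

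**Type I error, exact argument.**

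1. For an arm with facility proportions y1 and y2 and mean ȳ, the sandwich variance of the mean is Σ(yj − ȳ)²/4. The unbiased estimate is Σ(yj − ȳ)²/2. The sandwich is half of it.
2. The unbiased statistic for a two-arm contrast has 4 − 2 = 2 df. The Wald z is therefore √2 times a t on 2 df.
3. The test rejects when |t2| > 1.96/√2 = 1.386.
4. For 2 df, P(|t2| > c) = 1 − c/√(2 + c²). At 1.386 this is 1 − 1.386/√3.921 = 0.300.

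**Variants by the same formula.**

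| Variance | Reference | Type I error |
|---|---|---|
| Uncorrected sandwich | normal | 30.0% |
| Multiplied by 6/5 (six clusters) | normal | 26.8% |
| Multiplied by 4/3 (four clusters) | normal | 25.1% |
| Unbiased | normal | 18.9% |
| Uncorrected sandwich | t, 2 df (4.30) | 9.3% |
| Unbiased, pairwise | t, 3 df (3.18) | 8.6% |
| Unbiased, pairwise | t, 2 df (4.30) | 5.0% |

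**Simulation, no matching effect.** With 200,000 null trials per setting, 135 or 150 mothers per facility, prevalence 17%, 20% or 48% and CV 0 to 0.40, the uncorrected sandwich with normal quantiles rejected in 27.9% to 30.2%. At CV 0.25, 135 per facility and 20% prevalence it rejected in 29.6%. The chance that at least one of the two comparisons on one outcome is falsely significant was 46-47% (CV 0.05 to 0.25). In 600 actual GEE fits at 20% prevalence and CV 0.25, rejection was 29.3% to 31.7% (Monte Carlo error about 1.9 points).

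**Simulation, matching effective but ignored.** At 20% prevalence and CV 0.25, error falls from about 27% to 18% as the share of between-facility variance explained by matching goes from 25% to 90%. At CV 0.40 and 90% it is 14%.

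**Facility-level test.** Log facility proportions with variance pooled over six facilities have 6 − 3 = 3 df. Simulated type I error is about 5% without a matching effect and 2-4% if matching is effective and ignored. Power at CV 0.25 and 135 per facility is about 38% for 20% vs 40% and 16-17% for 20% vs 30%. The pairwise test on 2 df has about 28% and 13%.

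**The case against.** The strongest reply is that the protocol does not commit to an uncorrected sandwich or to normal quantiles, and that such details commonly sit in an analysis plan, which is not shown. That stands as far as the size is concerned: the 30% is conditional. It does not rescue the sentence, which claims validity on a single condition and omits the one this design fails to meet.

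Second, facilities are matched before randomization, and this lowers the error of an analysis that ignores matching. That also stands. The lowest figure found, 14%, is still nearly three times the nominal level and needs matching to explain 90% of the between-facility variance.

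Three stronger readings are tempting and not supported:

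- A reader might infer that a log-binomial model will also be run without GEE, ignoring clustering. The more natural reading is one log-binomial model fitted by GEE, since the next sentence concerns within-cluster dependence.
- A reader might take "Pearson chi-square will be used to compare categorical variables and T-test will be used for continuous variables" as a flaw in the primary analysis. Those tests do treat mothers as independent, but they only check baseline balance and do not touch the primary intervals.
- A reader might infer that any small-sample-corrected GEE can be referred to t on 3 df. For a pairwise contrast it cannot, because its variance uses only the two arms compared; that gives 8.6%.

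**Conclusion.** The concern holds. The statement that GEE inference is valid given a correct mean structure is wrong for two facilities per arm, and it governs the primary analysis, so it must be corrected. In the assumed usual form, type I error is about 30% per comparison without a matching effect, 25-27% with a software multiplier, and about 27% down to 18% at CV 0.25 with matching that is effective but ignored (14% at CV 0.40 and 90%). Across the settings simulated, prevalence, CV and the number of mothers per facility hardly change the unmatched figure, so recruiting more mothers in the same facilities is no cure. The documents do not support saying that the trial will have a 30% error rate: that depends on the variance and quantiles finally used and on how well matching works.

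**What to change.** Delete the validity sentence, or qualify it by stating that it requires many clusters and that this trial has two per arm. Make the primary analysis facility-level: take the log of each facility's proportion, compare arm means with residual variance pooled over all six facilities, use t on 3 df (critical value 3.18), and report prevalence ratios with confidence intervals. If a small-sample-corrected GEE is preferred for pairwise contrasts, refer it to t on 2 df (4.30). State whether matching enters the model. If it forms two sets of three facilities, one per arm (the protocol does not say), a term for the set leaves 6 − 3 − 1 = 2 df. As a minor side point, baseline data can be shown descriptively by facility and arm.

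The rewording is cheap, but the consequence is not. Intervals become much wider, and power is about 38% for 20% vs 40% and 16-17% for 20% vs 30% (3-df test, CV 0.25, 135 per facility). The power and cluster-number statements in the sample size paragraphs must be restated to match. No change of analysis removes the underlying limit of two facilities per arm.

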With more than half a million child deaths in 2008, DR Congo bears the third largest burden of child deaths worldwide (7). These deaths are the result of a web of complex determinants (18), yet results from the 2007 DHS in DRC provide enough evidence to believe that breastfeeding practices play a major role in the extremely high infant mortality rate in the country. First, of the 9.2% of infants who die before the age of one, 4.2% die during the neo-natal period and the remaining 5% between 1 and 12 months. More deaths in the post-natal period suggest that factors behind these deaths are to be found among other sources in the feeding practices. Second, DHS data also show that by the age of 6 months, more than 10% of children in DRC are already stunted, virtually 15% already underweight-for-age and approximately the same percentage emaciated. Third, though breastfeeding is nearly universally accepted (95% of children were breastfed at some point), only 48% of infants studied in the 2007 DHS were initiated on breastfeeding within 1 hour of birth, 18% received something other than breast milk before initiation of breastfeeding, and half received something other than breastfeeding at 1.4 months (19). Much of the supplementation that occurs in western Africa is water or traditional foods, and may be amenable to change if change is supported by a trusted advisor. Therefore these data have to be understood in the context of relatively high utilization of primary health care. In fact, despite the challenges to accessing health care in DR Congo, DHS data showed that 85% of pregnant women attended at least one antenatal visit, 70% of live births occurred in a health facility (97% in Kinshasa). Of children 12 to 23 months of age, 71%, 59%, 45% received the first, second and third doses of DPT immunization administered according to the WHO immunization schedule (20) and the DRC’s Expanded Program of Immunization at 6, 10, and 14 weeks, while 63% had been immunized against measles (at 9 months). In this context, interventions to promote and support early initiation and continued exclusive breastfeeding through 6 months integrated into the primary health care delivery system, particularly when bundled with well-child visits have the potential to substantially impact child undernutrion and its adverse consequences.

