Assuming a loss to follow-up rate of 10% over the 6 months - the duration of the follow-up in the study, the effective sample size that will be available for analysis is 135. With this effective sample size, our study will have an 88% power to detect a modest 30% increase in the prevalence of exclusive breastfeeding at 6 months in the intervention group – corresponding to a change as small as an increase from the current proportion of EBF at 6 months of 17% (assuming it stays the same in the usual care group) to 22.5% after implementing BFHI steps 1 through 9.

At the end of the evaluation, the findings of the study will be shared with all facilities that took part in the study and with the community. Facilities in the usual care arm will be encouraged to implement the most successful intervention.

1. **Sustainability and Potential for Scaling-Up**

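### Objective 1 does not have adequate power at the plan's own 17% usual-care rate: at most 72% for RR 1.5 ignoring clustering, and about 16% with the plan's own CV

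*Protocol*

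**What the plan says.** All the sizing text is in the Evaluation part of the Protocol's Proposal Narrative. The comparator for objective 1 is defined under Project Design and Implementation Plan as "continuation of current care practices (usual care").

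Three inputs describe the 6-month EBF rate in that one arm:

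- Power curves (Figure 2a): "various prevalence estimates of the prevalence of EBF at 6 months in the control group (15% to 35% for usual care"), with "a minimum expected effect size of RR = 1.5 for the first objective". The test is given as "Assuming two-tailed Person chi-square test with α values of .05", with no clustering term.
- Number of clusters (Figure 3): a CV of 0.25, clusters of 150, 80% power, "assuming a 20% prevalence of EBF in the usual care group".
- Loss-to-follow-up paragraph: "the current proportion of EBF at 6 months of 17% (assuming it stays the same in the usual care group").

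From the first of these the protocol concludes that 900 pairs should give adequate power to detect a modest difference between BFHI alone and usual care. It does not say at which control rate that holds. Six facilities are randomised to three groups, with 150 pairs per facility and 300 per group. The assumed 10% loss leaves 135 per facility.

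**The concern.** For a fixed risk ratio, the power of a chi-square test rises steeply with the control rate. A claim of adequacy over a range of 15% to 35% can therefore be true over much of the range and false at the rate that the investigators expect. Here the expected rate, 17%, is near the bottom of the range, where power is lowest. The claim also uses individual-level power, although facilities are randomised and the next paragraph supplies a between-facility CV.

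Objective 1 is one of two primary objectives, and the protocol means the results to inform scale-up. If power is overstated, a non-significant comparison could be read as evidence that BFHI steps 1-9 do not work, when the trial had little chance of showing an effect of the stated size.

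**Working it through.** **Inputs (Protocol, Evaluation, and Project Design and Implementation Plan).** Control rate p1 = 17%; RR 1.5, so p2 = 25.5%; two-sided α = 0.05; n = 300 per arm, or 2 × 135 = 270 after loss; CV k = 0.25; cluster size m = 150; six facilities in three groups, taken as c = 2 per arm.

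**1. The plan's own test, no clustering**

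Power = Φ{[(p2 − p1)√n − 1.96√(2p̄(1 − p̄))] / √(p1(1 − p1) + p2(1 − p2))}, where p̄ is the mean of p1 and p2.

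- n = 300: (1.472 − 1.134)/0.575 = 0.588, power 72%.
- n = 270: (1.397 − 1.134)/0.575 = 0.457, power 68%.

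| Control rate | 300 per arm | 270 per arm |
|---|---|---|
| 15% | 65% | 61% |
| 17% | 72% | 68% |
| 20% | 81% | 77% |
| 25% | 91% | 88% |
| 35% | 99% | 98% |

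Power reaches 80% at a control rate of 19.7% (300 per arm) or 21.3% (270 per arm).

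**2. The plan's cluster formula, reproduced first**

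Hayes-Bennett, unmatched: c = 1 + 7.849 × [(p1(1 − p1) + p2(1 − p2))/m + k²(p1² + p2²)] / (p2 − p1)².

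For 20% against 40%: 1 + 7.849 × (0.00267 + 0.01250)/0.04 = 3.98. This matches the protocol's statement that fewer than 4 clusters are needed, and the formula counts clusters per arm.

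**3. The same formula at 17% and RR 1.5**

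- Clusters needed: 1 + 7.849 × (0.00221 + 0.00587)/0.007225 = 9.8 per arm, against 2 planned. At 20% it is 9.3, and at 35% it is 8.2.
- Power with 2 per arm: Φ{√[(c − 1)(p2 − p1)²/(0.00221 + 0.00587)] − 1.96} = Φ(0.946 − 1.96) = 16%.
- Without the +1 term (c in place of c − 1): Φ(1.338 − 1.96) = 27%.

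| Control rate | Power, 2 × 150 per arm | Without +1 term |
|---|---|---|
| 15% | 15% | 26% |
| 17% | 16% | 27% |
| 20% | 16% | 28% |
| 25% | 17% | 29% |
| 35% | 18% | 31% |

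With 135 per facility, the values at 17% are 15% and 26%. The between-facility term (0.00587) dominates the sampling term (0.00221), so the control rate and the 10% loss hardly matter once clustering is counted.

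**The case against.** Several points on the other side are sound.

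- **A reader might infer that 15-35% contradicts 17%.** It does not. The protocol presents the range as various estimates, 17% lies inside it, and a range wider than the point estimate is ordinary sizing practice. The defect is that the conclusion is not tied to the expected rate. Nor can it be shown that the upper part of the range produced the conclusion, since the plotted curves were not available to check.
- **A reader might infer from the Background that the true 6-month rate is well below 17%**, because "half received something other than breastfeeding at 1.4 months". That figure is the age by which half had stopped exclusive breastfeeding, not a 6-month prevalence. Moving from one to the other needs an assumed stopping pattern that the protocol does not give. The figure is also national, whereas the trial enrols Kinshasa mothers who intend to attend well-baby visits. It is compatible with 17%.
- **The gap between 20% and 17% in the cluster count is small:** 9.3 against 9.8 clusters per arm at RR 1.5.
- **A reader might infer that power is adequate once the control rate passes about 20%.** That holds only for the unclustered test. With the plan's CV, no rate from 15% to 35% comes near 80%.
- **The protocol does claim power at 17%:** 88% for a rise to 22.5%. This does not rescue the adequacy claim. With 270 per arm the same chi-square gives (0.904 − 1.103)/0.562 = −0.356, or 36%. A value of 88% does appear for 45% against 58.5%, the low end of the objective 2 inputs ("EBF at 6 months in the BFHI steps 1-9 group of 45 to 65% and a minimum expected effect size of RR = 1.3"). That misstatement is a separate correction.
- **Facilities are to be matched, which could lower the effective CV.** True, but no matched CV is given, and the protocol's own cluster statement reproduces with the unmatched formula. Even a CV of zero would not take power at 17% above the unclustered 72%.

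**Conclusion.** The point holds in a limited but firm form. At the usual-care rate that the protocol itself assumes, adequate power for objective 1 at RR 1.5 is not delivered: 72% before losses and 68% after, under a test that ignores the randomisation unit. Counting clustering with the plan's own CV, power is about 16% at 17% and 15-18% across the whole 15-35% range (about 26-31% without the +1 term).

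The unclustered figures rest only on the protocol's stated inputs. The clustered figures also assume an equal split of two facilities per arm and the unmatched Hayes-Bennett formula with a normal approximation. With so few clusters they indicate scale rather than exact power. The point does not rest on the 15-35% range being wrong or on any rate derived from the 1.4-month figure.

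**What to change.** - Use 17% as the base-case usual-care rate in Figure 2a, Figure 3 and the loss-to-follow-up paragraph. Keep the rest of the 15-35% range, labelled as sensitivity.
- Replace the adequacy statement for objective 1 with the power at 17% and RR 1.5. Lead with the clustered value (CV 0.25, two facilities of 150 per arm): about 16%, or about 27% without the +1 term. Give 72% (300 per arm) and 68% (270 per arm) only as an upper bound that ignores clustering. Printing 68-72% alone would still mislead.
- State that the Hayes-Bennett count in Figure 3 is per arm, and set it beside the two facilities per arm planned.

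The cost is protocol wording and a re-run of existing calculations, with no extra mothers or facilities. The stated power becomes much less favourable. Whether to respond by changing the number of facilities is a separate design decision.
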